However, in our study, cluster effects may appear for subjects within identical training groups: We expect 700 included subjects participating in 170 different training courses. Thus four participants of each training group will averagely be subjects of the study (whereas the rest of the group participants are no study subjects). With a rather high intra class correlation of 0.33 we obtain a variance inflation factor of 2 for the intervention. Therefore, with 700 subjects per study arm the aimed power should be reached.

We refrain from analyzing our data using a matched-pair design as propensity score matching does not guarantee that individual pairs will be well-matched on the full set of covariates, only that groups of individuals with similar propensity scores will have similar covariate distributions [33]. Despite this fact, propensity score matching including among other variables baseline WOMAC scores as matching factors may reduce variance of outcome measures and therefore probably increase the power of the study further if the propensity score is included as covariate in the statistical evaluation model. However, it is difficult to quantify this effect and thus we conservatively calculated the sample size obtained for the parallel group design with cluster effect as described in the preceding paragraph.

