Sum of specific diagnosis (hip/knee OA) related health care costs in the last 6 month prior t0 (tm6): Sick-pay, hospital costs, out-patient costs, costs related to periods of disability and costs related to disease related drugs, physical modalities and adjuvants such as walkers, cranks or orthotics.	+/− 100 EUR
Disability days in the last 24 month prior t0 (tm24)	+/− 1 Day
Disability days in the last 6 month prior t0 (tm6)	+/− 1 Day
Specific disability days (hip/knee OA) days in the last 24 month prior t0 (tm24)	+/− 1 Day
Specific disability days (hip/knee OA) in the last 6 month prior t0 (tm6)	+/− 1 Day

Legend: a tolerance of “0” is equal to complete agreement, i.e. for age in years. Matching criteria are derived from the insurance data base

The matching process for the identification of statistical controls (CO) for each subject of the intervention group will be permuted in blocks: The matching procedure will be conducted quarterly until the number of needed subjects is reached.

Selected subjects will be asked for study participation (see section recruiting). The final statistical twins for each participant (1:1 matching) will be selected from all eligible responders. As a primary criterion, twins must be identical with regard to site(s) of OA (hip, knee or both). The following independent variables of the self-administered questionnaires (SAQ) and insurance data base (IDB) will then be used as input variables for the logistic regression of the PSM:Socio-demographic data at t0: age and gender (SAQ)Co-morbidity: Quantity of hierarchical ordered morbidity groups in the previous year (IDB)Osteoarthritis of the hip or knee in the previous year (IDB)WOMAC Index subscale pain at t0 (SAQ).WOMAC Index subscale physical functioning at t0 (SAQ).Quality Adjusted Life Years at t0 via VR-6D (SAQ).Body mass index at t0 (SAQ).Joint replacement hip and/or knee joint(s) at t0 (SAQ).General Self-Efficacy scale GSE at t0 (SAQ)Habitual physical and sports activity status at t0Participation in health activity programs (i.e. walking courses) at t0

If there are any cost/disability day categories, in which the standard mean differences after matching are above 0.05, a new matching will be conducted with these cost/disability day categories as matching variables in addition. No follow-up data will be analyzed prior to the final definition of the statistical twin of the CO for a given IG patient.

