The finally defined controls and cases will be included into a linear model with the propensity score as covariate. Additionally, we will use models for longitudinal data using each measurement point (instead of only t0 and t3 for the primary analysis). The level of significance will be 0.025 for primary endpoints. Secondary endpoints will be analyzed analogously without claiming confirmatory interpretation of *p*-values.

Descriptive analysis will include absolute and percentage frequencies for categorical variables, means, medians, standard deviations, quartiles and ranges for quantitative variables and medians, quartiles and ranges for ordinal variables. For the main results, two-sided 95 % confidence limits will be given additionally to significance tests. For percentages exact confidence interval for proportions based on the binomial distribution will be given.

Exploratory, prognostic factors will be analyzed using multiple regression models (linear regression) to identify potential responders to the training.

Correlation analyses will use Pearson product moment correlation coefficient (normally distributed variables) and Spearman correlation (non-normally distributed variables).

The primary analysis will be done on the full set of patients recruited in consideration of the exclusion criteria “limited pain and impairment in physical function” (WOMAC Index subscales pain and physical function with values below 15) except for patients refusing consent during the study and obviously wrongly diagnosed patients. A secondary analysis will be done using the full set of eligible and included patients irrespective of their limitations in pain and physical function at baseline (t0). This secondary analysis will only claim confirmatory interpretation of p-values if the primary analysis is able to detect group differences in a statistical manner. Otherwise the secondary analysis will be done in an explorative manner.

Missing values will be imputed using multiple imputation approaches, complete case and last observation forward analysis will be performed as a sensitivity analysis. No interim analysis, except for administrative purposes will be performed. All statistical analysis will be done using the software SPSS and R in the newest release.

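### Baseline WOMAC acts on the primary comparison only through the propensity score (and possibly a change score): the model names no direct t0 covariate, and the one re-matching trigger ignores WOMAC

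*Protocol article*

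**What the plan says.** The section on matching procedures and statistical analysis of clinical endpoints gives the primary model: the matched subjects are to be "included into a linear model with the propensity score as covariate". No further covariate is named. The dependent variable is not stated either. The section says only that the primary analysis uses t0 and t3, and the Sample size section works with within-person differences.

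Both WOMAC subscales at t0 are inputs to the logistic regression for the propensity score. The Sample size section says that "propensity score matching including among other variables baseline WOMAC scores as matching factors may reduce variance of outcome measures" and that this would "therefore probably increase the power of the study further if the propensity score is included as covariate in the statistical evaluation model".

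One numeric balance rule is given: "If there are any cost/disability day categories, in which the standard mean differences after matching are above 0.05, a new matching will be conducted", with the offending categories added as matching variables. No rule is stated for WOMAC or for any other input to the score.

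The exclusion for WOMAC pain and function below 15 applies to the primary analysis only (footnote to Table 1). The article does not say whether matching comes before or after it.

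**The concern.** The comparison is not randomised, and the two primary endpoints are WOMAC subscales, so their t0 values are the covariates one would most want balanced and in the model. A propensity score is built to predict participation, not outcome. Once groups are matched on it, it has little left to explain in the outcome, so it is a weak substitute for the t0 value as a source of precision.

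The balance rule has a related gap. The first-stage criteria in Table 5 all come from the insurance data base, so WOMAC balance rests wholly on the second-stage score. If a cost category exceeds 0.05, the score is refitted with more variables and the twins change. WOMAC balance could get worse at that step, and nothing stated would respond.

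**Working it through.** **1. The plan's own figures.** With effect size 0.3, two-sided alpha 0.025 and power 0.90, the normal approximation gives 276 per group and the noncentral t gives 278, as stated. Drop-out: 278/0.80 = 347.5, so 348 (stated 350). Clustering: 1 + (4 − 1) × 0.33 = 1.99 (stated 2), hence 700. None of this relies on a gain from the score covariate.

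**2. Planning scale.** The change SDs for pain in the earlier randomised trial are 13.9 and 15.3. The pooled SD is √((13.9² + 15.3²)/2) = 14.6, so the planned effect is 0.3 × 14.6 = 4.4 points.

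**3. Assumption.** The baseline-to-t3 correlation r is not in the article. I take 0.5 to 0.8, with equal SDs at both times.

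**4. Precision without any propensity covariate.** Adjusting for the t0 value leaves (1 + r)/2 of the change-score variance and 1 − r² of the t3-score variance.

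| r | against change | against t3 | 278 × (1 + r)/2 |
|---|---|---|---|
| 0.5 | 0.75 | 0.75 | 209 |
| 0.6 | 0.80 | 0.64 | 223 |
| 0.7 | 0.85 | 0.51 | 237 |
| 0.8 | 0.90 | 0.36 | 251 |

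The change cannot raise the sample size. These ratios overstate the gain here, because the planned model already holds the score.

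**5. Precision against the planned model.** Three simulations of 1:1 matching under assumed inputs gave these standard errors. B and C used 700 treated, nearest-neighbour matching, 4 controls per case and a pre-match WOMAC difference of 0.3 SD.

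| Simulation | change + score | t3 + score | t3 + score + t0 value |
|---|---|---|---|
| A, r = 0.6 | 0.0617 | – | 0.0567 |
| B, r = 0.6 | 0.0454 | 0.0488 | 0.0427 |
| C, r = 0.7 | 0.0405 | 0.0495 | 0.0382 |

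- Against change + score: 1 − (0.0567/0.0617)² = 16% (A), 1 − (0.0427/0.0454)² = 12% (B), 1 − (0.0382/0.0405)² = 11% (C).
- Against t3 + score: 1 − (0.0427/0.0488)² = 23% (B), 1 − (0.0382/0.0495)² = 40% (C).
- The score alone, added to a change-score model: 1 − (0.0617/0.0633)² = 5% (A), 1 − (0.0454/0.0476)² = 9% (B).

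These are model-based errors, which set the test and the interval. In C the spread of the estimates over 200 runs was 0.0397, 0.0443 and 0.0392. On that measure the cut is only about 3% against change + score and 22% against t3 + score. Matching has already taken part of the gain, and a model for unmatched groups does not credit it.

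**6. Effect of a leftover baseline difference d (in SDs), before any correction by the score covariate.** The baseline SD implied by a change SD of 14.6 is 14.6/√(2(1 − r)). The shift is d × SD × (1 − r) on a change score and d × SD × r on the t3 score. For d = 0.1:

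| r | SD | change: points (share of 4.4) | t3: points (share of 4.4) |
|---|---|---|---|
| 0.5 | 14.6 | 0.73 (17%) | 0.73 (17%) |
| 0.6 | 16.3 | 0.65 (15%) | 0.98 (22%) |
| 0.7 | 18.9 | 0.57 (13%) | 1.32 (30%) |

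At r = 0.8 the change-score share falls to 11%. If the planned effect is read as 0.3 SD of the t3 score instead, the t3 share is 0.1 × r/0.3, or 17–27% for r from 0.5 to 0.8. On the points scale the t3 share grows with r, so the 30% is tied to r = 0.7.

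**7. Would such a difference survive?**
- With a correctly specified score (C), the mean WOMAC difference after matching was about 0.002 (SD about 0.026). It exceeded 0.05 in about 7% of runs and 0.10 in none. Bias was about −0.004 SD.
- Re-matching with 8 added cost variables (set-up B) raised the chance of a WOMAC difference above 0.05 from 2% to 7% with 4 controls per case, and from 5% to 16% with 2.
- Dropping low WOMAC scorers after matching raised it from 2% to 17%. If WOMAC was also less spread out in the intervention group, which a linear score misses, it rose from 6% to 90% (mean difference −0.09).

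The levels depend on the set-up: C gave 7% without re-matching where B gave 2%. Only the direction should be relied on.

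**The case against.** A reader might infer that baseline WOMAC is not adjusted for at all. The article does not support that. Both subscales are in the score, which drives the matching and is also the covariate, and a change score (a natural reading of the Sample size section) would use t0 directly.

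A reader might also take the caveat about poorly matched pairs as an admission of imbalance. The same sentence says that groups with similar scores will have similar covariate distributions, and bias in a group comparison depends on groups. The caveat is the reason for not using a paired analysis.

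The cost rule has its own logic. Cost and disability-day variables are absent from the initial input list, so they need a separate check, and any re-matching keeps WOMAC in the score. The hoped-for power gain is hedged, and the sample size was set without it. A full balance table may sit in a fuller plan, so it does not follow that WOMAC balance will go unexamined. That baseline WOMAC is the strongest predictor of outcome is plausible but nowhere stated.

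All of this stands, and it removes any claim that the planned estimate is biased. It does not answer the narrower point. The article does fix the model and a numeric trigger, and as fixed the first has no direct t0 term and the second does not react to WOMAC.

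**Conclusion.** The point holds as a recommendation on efficiency and safeguards, and it should be made. With a well-specified score and good overlap, the loss is mainly precision: about 11–16% of model-based variance against change + score and about 23% or more against t3 + score, at assumed r of 0.6 to 0.7. Less of this shows in the true sampling spread against change + score.

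The shift of 11–17% (change) or up to about 30% (t3) of the planned effect is conditional. It supposes a leftover difference of 0.1, which did not occur with a correctly specified score. It becomes realistic with a misspecified score, poor overlap, or the WOMAC below 15 exclusion applied after matching, and in those cases the stated rule would not react. The correlation and all simulation inputs are assumptions.

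**What to change.** - State the primary model in full: t3 WOMAC subscale on group, propensity score and the t0 value of the same subscale, fitted separately for pain and function.
- Apply the 0.05 threshold to all propensity-score inputs, at the least to WOMAC pain and function at t0, and repeat the check after any re-matching on cost variables.
- Evaluate it in the set used for the primary analysis, after the WOMAC below 15 exclusion, and state whether that exclusion precedes the matching.
- Complete these steps before any follow-up data are seen, as the plan already requires for the definition of twins.

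The cost is wording only. All variables are already collected at t0, the sample size does not rise, and the blinding of the matching statistician to follow-up data is unaffected.

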
### Statistics

#### Sample size

Below are given details on the sample size estimation for primary clinical outcomes. However, aside from statistical power, a sufficiently large sample is necessary to obtain representative results for the general population and to allow sustainable statements on the effectiveness and efficiency of the intervention for secondary clinical as well as economic outcomes. We therefore plan to include all eligible patients willing to participate in the study and finally assume a number of n = 700 in each group. This number takes into consideration the degree of capacity utilization of hip and knee training courses as well as the number of subjects non eligible due to inclusion- and exclusion criteria as well as subjects refusing consent to participate in the study (Fig. 1).

The empirical basis of the sample size estimation for primary outcomes was retrieved from the paper by Krauss et al. [17]. In this randomized controlled trial (RCT), intra-individual differences of WOMAC subscale pain and WOMAC subscale physical function identically showed an effect size of about 0.5 between the intervention and the control group (pain, intervention: −8.5 ± 13.9, control: −1.3 ± 15.3, physical function, intervention: −8.4 ± 13.4, control: −2.1 ± 12.9).

Based on the previous results of the RCT and the so-called efficacy-effectiveness gap between RCTs and studies under real life conditions [32] we finally assume an effect size of ES = 0.3.

Due to the fact that we want to test the two endpoints (pain and physical function) simultaneously and without hierarchical order, we choose a level of significance of 0.025 (two-sided, Bonferroni correction) and a power of 0.90. This leads to a sample size of 278 subjects per group in the parallel group design without cluster effects (nquery release 7.0). The drop-out rate in the intervention group of the above mentioned RCT was 8 % [17]. As this value is quite low, we assume a somewhat higher number of non-finishers and estimate the rate to be 20 %. Thus 350 subjects should be allocated to each treatment arm.

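### The two primary endpoints are tested at two-sided 0.025, but the main results are given with 95 % limits not labelled as unadjusted, so an interval can exclude zero for an endpoint that fails its test

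*Protocol article*

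**What the plan says.** Under Sample size, the protocol article says that "we want to test the two endpoints (pain and physical function) simultaneously and without hierarchical order", and for that reason "we choose a level of significance of 0.025 (two-sided, Bonferroni correction) and a power of 0.90". Under Matching procedures and statistical analysis of clinical endpoints, the level is repeated: "The level of significance will be 0.025 for primary endpoints". The next paragraph of that section turns to descriptive statistics and includes the sentence "For the main results, two-sided 95 % confidence limits will be given additionally to significance tests".

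The article does not define what counts as a main result. It nowhere mentions a 97.5 % or multiplicity-adjusted interval, and nowhere describes the 95 % limits as unadjusted or descriptive. Secondary endpoints are to be analysed in the same way, but without confirmatory interpretation.

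**The concern.** A two-sided test at level α agrees with a two-sided interval at level 1 − α: the test rejects exactly when the interval excludes zero. At α = 0.025 that interval is 97.5 %. The plan fixes 0.025 for the tests and 95 % for the limits beside them, so the two need not agree.

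Many readers look first at the interval. If p for pain were 0.03, the publication would show a 95 % interval clear of zero next to a test that is not significant by the plan's own rule, and the plan has no sentence telling the reader how to take the pair. The Bonferroni split was adopted because either endpoint alone can carry a claim, and it was paid for in sample size. Intervals at the uncorrected level blur that protection in the report. The point also touches a later step: the confirmatory status of the analysis without the WOMAC threshold of 15 depends on whether the primary analysis detects a group difference, so it should be beyond doubt what counts as detection.

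**Working it through.** **Inputs.** From Sample size: two primary endpoints, two-sided α = 0.025 each, power 0.90, "we finally assume an effect size of ES = 0.3", 278 per group before dropout and clustering, dropout 20 %, and 700 planned per group. From the clustering paragraph of the same section: about 4 study subjects per course, intraclass correlation 0.33, and a variance inflation of 2 stated for the intervention. From the analysis section: α = 0.025 again, and 95 % limits.

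**1. The plan's own figure.** With the noncentral t for a two-sample comparison at standardised effect 0.3 and two-sided α = 0.025, power is 0.8999 at 277 per group and 0.9010 at 278. The stated 278 is reproduced. The normal formula gives 276 at 0.025 and 234 at 0.05, so the design does use 0.025. Dropout: 278 / (1 − 0.20) = 347.5, stated as 350. Total α: 2 × 0.025 = 0.05.

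**2. Width.** Half-width is z × SE. For 95 %, z = 1.960; for 97.5 %, z = 2.241. The ratio is 2.2414 / 1.9600 = 1.144, so the matching limits are 14 % wider.

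**3. Where interval and test part.** The 95 % interval excludes zero while the 0.025 test fails when 1.960 < |z| < 2.241, that is, when 0.025 < p < 0.05. Example at 278 per group without clustering, in SD units: SE = √(2/278) = 0.0848. The window is an observed effect from 1.960 × 0.0848 = 0.166 to 2.241 × 0.0848 = 0.190. At p = 0.03 the estimate is 0.184, the 95 % interval is 0.018 to 0.350, and the 97.5 % interval is −0.006 to 0.374.

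**4. How often, under no effect.** 0.05 − 0.025 = 0.025 per endpoint, at any sample size.

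**5. How often, at effect size 0.3.** The chance is the power at 0.05 minus the power at 0.025. The planned trial has 700 per group; less 20 % dropout, 700 × 0.80 = 560 are analysed. The stated inflation is 1 + (4 − 1) × 0.33 = 1.99, taken as 2. With inflation V₁ in the intervention arm and V₂ in the control arm, SE = √((V₁ + V₂)/560). Noncentral t with 1118 degrees of freedom:

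| Case (560 per group) | SE | Power at 0.05 | Power at 0.025 | Discordant |
|---|---|---|---|---|
| No clustering (V₁ = V₂ = 1) | 0.0598 | 99.9 % | 99.7 % | 0.2 % |
| Inflation in intervention arm only (V₁ = 2, V₂ = 1) | 0.0732 | 98.4 % | 96.8 % | 1.6 % |
| Inflation in both arms (V₁ = V₂ = 2) | 0.0845 | 94.4 % | 90.4 % | 4.0 % |

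At the bare minimum of 278 per group without clustering, the same calculation gives 94.2 % − 90.1 % = 4.1 %. That figure belongs to the smaller sample, not to the trial as planned.

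**The case against.** The strongest defence is that no inferential rule is wrong. Significance is decided by the 0.025 tests, and the limits are given in addition to them. No sentence says that an interval excluding zero establishes an endpoint. The sentence on limits stands in the paragraph on descriptive analysis, so it can be read as ordinary estimation. Unadjusted 95 % intervals beside multiplicity-adjusted tests are a legitimate way to report, and an article may leave such wording to a fuller document.

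Most of this stands and limits the point. Three stronger readings that a reader might draw are not supported:

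- That the error control of the primary analysis is broken. It is not: the tests use 0.025 each, and 2 × 0.025 = 0.05.
- That the 95 % intervals have the wrong coverage. Each keeps its nominal 95 % for its own parameter. Two of them guarantee only 90 % jointly by the Bonferroni bound, but the plan never promises joint coverage.
- That roughly 4 % discordance is the general expectation at effect size 0.3. At the planned size it is reached only with inflation of 2 in both arms, whereas the article states the inflation for the intervention and calls the intraclass correlation rather high.

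What does not stand is the appeal to missing detail. The article states both levels, they do not match, and the 95 % limits carry no label. Main results is undefined, but a reading that leaves out the two primary endpoints is hard to sustain, since the limits accompany significance tests and the primary endpoints are the principal confirmatory ones.

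**Conclusion.** The point holds as a mismatch between the stated test level and the stated interval level for both primary endpoints. It concerns reporting and interpretation; type I error, power and sample size of the tests are as planned. A discordant pair has a chance per endpoint of 2.5 % under no effect and of about 0.2 % to 4.0 % at effect size 0.3, depending on clustering.

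This rests on taking the main results to include the primary endpoints, on 560 analysed per group (700 less 20 %), and on a simple two-group comparison with the stated inflation of 2. The propensity-score covariate and multiple imputation would change the standard error, but not the width ratio or the range of p in which test and interval disagree.

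**What to change.** Replace the sentence on confidence limits with wording such as: *For the two primary endpoints, two-sided 97.5 % confidence limits are reported, matching the 0.025 significance level; two-sided 95 % limits are reported for non-confirmatory results. If 95 % limits are also shown for the primary endpoints, they are labelled as unadjusted and do not decide significance.*

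The cost is this change of wording and primary-endpoint intervals that are 14 % wider. No test, sample size or data collection changes.

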### Outcome measures (Table 4, Fig. 5)

**Table 4 Tab4:** Outcome measures

Characteristics & confounders	Description and instrument	Data source	Sample	Collection points
Patient’s characteristics	Date of birth, gender, ethnicity, BMI (height, weight), site (s) of OA diagnosis, date of first OA diagnosis, labour situation (working, retired, unemployed, in rehabilitation status)	SAQ, IDB	IG, CO	t0, t3, t6, t12, t24
Primary outcome measure	Clinical Outcomes			
Pain	WOMAC Index 3.1 German (11-box NRS): subscale pain	SAQ	IG, CO	t0, t3
Function	WOMAC Index 3.1 German (11-box NRS): subscale physical functioning	SAQ	IG, CO	t0, t3
Secondary outcome measures	Clinical Outcomes		IG, CO	
Stiffness, disease specific impairment	WOMAC Index 3.1 German (11-box NRS): subscale stiffness, overall score	SAQ	IG, CO	t0, t3, t6, t12, t24
Pain, physical function	WOMAC Index 3.1 German (11-box NRS): subscale pain, subscale physical function	SAQ	IG, CO	t6, t12, t24
Health related quality of life	VR-12 incl. VR-6D utility index (4-week-time-slot)	SAQ	IG, CO	t0, t3, t6, t12, t24
General Self-Efficacy	General self-efficacy scale (GSE)	SAQ	IG, CO	t0, t3, t6, t12, t24
Response to exercise	Omeract-OARSI Set of Responder Criteria: composite score with minimum absolute and relative change levels for pain or pain & function	SAQ	IG, CO	t0, t3, t6, t12, t24
Physical activity status	Habitual physical and sports activity status	SAQ	IG, CO	t0, t3, t6, t12, t24
Time to surgery	Endpoint “elective joint replacement”	IDB	IG, CO	t0, t3, t6, t12, t24
	Patient satisfaction			
	Modified version of the ZUF-8 Questionnaire to assess patient satisfaction	SAQ	IG	t3
	Economic data			
Unspecific and specific (OA-related) health care costs	Out-patient costs, hospital costs, costs related to drugs, adjuvants and physical modalities, rehabilitation costs, sick-pay	IDB	IG, CO	tm24, tm18, tm12, tm6 t0, t3, t6, t12, t24
Unspecific/specific (OA related) periods of disability	Days of disability (overall and related to OA)	IDB	IG, CO	tm24, tm18, tm12, tm6 t0, t3, t6, t12, t24
Intervention related costs	Costs for human and physical resources/session	IDB	IG	t3, t6, t12, t24
	Adherence to exercise			
Training adherence	Summarized number of attended training sessions according to training log	SAQ	IG	t3
	Safety evaluation			
Adverse events and side-effects	Summarized number and details of adverse events and side-effects according to training log	SAQ	IG	t3

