(II) Our follow-up data will be gathered up to 2 years after the initiation of the supervised exercise intervention and will therefore give information on clinical and economic outcomes in the long-term.

(III) The intervention program of this study is predefined and we do not differentiate between different dosages. Nonetheless data on adherence to exercise can be related to effect size and may allow an interpretation on continuity of an exercise intervention in relation to response, whereby confounders for exercise adherence such as pain or dissatisfaction with the intervention etc. have to be considered as well. Another aspect that is related to exercise dosage is the possibility to compare results of this study to other interventions with different exercise frequencies, intensities, times and types of intervention (FITT). This comparison may therefore contribute to the knowledge gained with respect to dose–response relationships of exercise interventions in OA.

(IV) Aside from the comparison of different interventions in general, an individual perspective may gather new knowledge in terms of personal contextual factors that are related to intervention outcome. Identification of possible predictors of treatment responsiveness is therefore another important issue of this research. For example data of previous studies report a gender-specific response to exercise [34, 35]. Additional confounders may be related to baseline pain level, self-efficacy, socio-demographic data etc. In the context of this study, a responder analysis will be conducted according to the OMERACT-OARSI Set of responder criteria [25]. A sub-analysis comparing personal contextual factors of responders versus non-responders may allow a better understanding of relevant prerequisites for successful exercise participation and therefore facilitate individualized treatment recommendations in OA.

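### The exploratory search for responders to the training is framed as a prognostic analysis with no stated contrast to the matched controls, so natural course and regression to the mean can be read as treatment response

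*Protocol article*

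**What the plan says.** Under 'Matching procedures and statistical analysis of clinical endpoints' the article states, as an exploratory analysis, that "prognostic factors will be analyzed using multiple regression models (linear regression) to identify potential responders to the training". The outcome, the sample (intervention group only or both groups) and the model terms are not given.

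Discussion item (IV) gives the purpose: "Identification of possible predictors of treatment responsiveness is therefore another important issue of this research". It names candidate factors: "Additional confounders may be related to baseline pain level, self-efficacy, socio-demographic data etc". It announces a responder analysis by the OMERACT-OARSI criteria and then: "A sub-analysis comparing personal contextual factors of responders versus non-responders may allow a better understanding of relevant prerequisites for successful exercise participation". The hoped-for use is to "facilitate individualized treatment recommendations in OA".

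Table 4 describes the responder criterion as a "composite score with minimum absolute and relative change levels for pain or pain & function", that is, a change within the person, and lists it for both the intervention and the control group. The only model structure set out in the statistics section is that of the main analysis: "The finally defined controls and cases will be included into a linear model with the propensity score as covariate". No group-by-factor term appears anywhere.

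**The concern.** A factor that predicts improvement among trained patients is prognostic. It marks a responder to the training only if the difference between trained and control patients changes with the factor. The article names a method for the first question and attaches to it an inference that belongs to the second.

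The design makes the distinction matter. Patients enter on a physician's referral for hip or knee complaints. The primary analysis set leaves out those scoring below 15 on both WOMAC subscales. Response is defined by change from baseline. All three favour apparent improvement in patients who start with high pain, whether or not they train. Baseline pain, one of the candidate factors, is therefore the one most exposed. At stake is whether advice on who should be offered the program would rest on effect modification or on the ordinary course of the disease.

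**Working it through.** The article gives no figure for the responder analysis, so there is none to reproduce there. The sample size for the primary outcomes does reproduce: effect size 0.3, two-sided 0.025 and power 0.90 give 276 per group by the normal formula and 278 by the exact t calculation, as stated.

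**1. How many controls meet a responder cut-off?** Inputs from 'Sample size' (earlier trial, pain change): trained -8.5 ± 13.9, control -1.3 ± 15.3. Assumptions: normal changes and a single absolute cut-off c, for illustration. P(fall of at least c) = Φ((-c - mean)/SD).

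- c = 10, trained: Φ((-10 + 8.5)/13.9) = Φ(-0.108) = 0.457
- c = 10, control: Φ((-10 + 1.3)/15.3) = Φ(-0.569) = 0.285
- Ratio control/trained: 0.285/0.457 = 0.62

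| Cut-off | Trained | Control | Ratio |
|---|---|---|---|
| 5 | 0.599 | 0.404 | 0.67 |
| 10 | 0.457 | 0.285 | 0.62 |
| 15 | 0.320 | 0.185 | 0.58 |
| 20 | 0.204 | 0.111 | 0.54 |

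The function changes (-8.4 ± 13.4 and -2.1 ± 12.9) give ratios of 0.68 down to 0.43 over the same cut-offs.

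**2. How strongly does baseline pain predict change with no training effect?** Assume equal SDs at baseline and 3 months and correlation ρ between them. Then corr(change, baseline) = -√((1 - ρ)/2).

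- ρ = 0.5: -√0.25 = -0.50
- ρ = 0.8: -√0.10 = -0.32

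With t = r√((n - 2)/(1 - r²)), n = 560 (700 less 20% drop-out) gives t = -13.6 and -7.9. Halving n to 280, for the plan's own variance inflation factor of 2, gives -9.6 and -5.6. Baseline pain would be flagged in every case.

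**3. Does a group-by-factor term remove the artefact?** Simulation, 2,000 runs per setting, with the same training effect (0.3 SD of change) in everyone and no true modifier. Assumed: change SD 15, baseline SD 15 or 20, 280 or 560 per group, cut-off 10 points, tests at 5%.

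| Analysis | Runs flagging baseline pain |
|---|---|
| Change on baseline, trained group only | 100% |
| Responders v. non-responders, trained group only | 99.8 to 100% |
| Group-by-baseline term, both groups | 4.6 to 5.6% |

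The first two find a predictor of response where none exists. The interaction keeps its nominal error rate.

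**4. What does the interaction cost in power?** For a factor that splits each group 50/50, there are four cells of n/2. The interaction has SE = √(4/(n/2)) = √(8/n) in SD units, and power is about Φ(δ/SE - 1.96).

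- n = 280, δ = 0.3: SE = 0.169, power 0.43
- n = 560, δ = 0.3: SE = 0.120, power 0.71
- n = 280, δ = 0.6: power 0.94

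The 280 is pessimistic, because the plan applies the inflation to the intervention group only.

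**The case against.** The strongest reply is that a specification is being read out of silence. The regression gets one sentence in a journal article. A multiple regression can contain interactions, and their listing could be left to an analysis plan that is not shown. Table 4 collects responder status in both groups, and secondary endpoints are to be analysed like the primary ones, so responder rates may well be compared between groups. The analysis is labelled exploratory, the factors are already called prognostic, and the Discussion says only that the comparison may help.

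Much of this stands. A reader might infer that the control group is never used for this question. The document does not say so; it leaves the sample open. A reader might also infer that artefacts are bound to be reported as treatment response, or that treatment recommendations will be drawn directly from this analysis. The exploratory label and the hedged wording do not support that.

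The 62% likewise invites the reading that this share of responders would have improved untrained. It is a ratio of two group rates, and it is a share of individuals only if training prevents nobody's response. It also rests on one pain cut-off where the planned criterion is a composite, and on a 12-week trial in hip patients only. The correlation result concerns baseline pain; gender, self-efficacy and socio-demographic factors are not tied to change in the same mechanical way, and nothing is quantified for them.

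What does not stand is that this is merely an omitted detail. The article names both the method and the conclusion it should serve, and the two do not fit. Pooling both groups with main effects only would not repair that, and the exploratory label does not turn a prognostic estimate into an answer about treatment response.

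**Conclusion.** The concern holds in a limited form. The article pairs a prognostic regression and a responder comparison with a question about effect modification, and states no contrast with the matched controls for it. In the intervention group alone, or pooled with main effects only, these analyses can mistake natural course and regression to the mean for response to training, most clearly for baseline pain.

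On the earlier trial's pain figures the control response rate is 54 to 67% of the trained rate for cut-offs of 20 to 5 points, given normality. Without any training effect, baseline pain would correlate -0.50 to -0.32 with change, given equal SDs and a correlation of 0.5 to 0.8 between the two measurements. That correlation, the cut-offs and the baseline SDs in the simulation are assumptions, because the article does not give them. Primary endpoints, significance level and sample size are untouched. The point is worth correcting because the Discussion treats the question as important and links it to individualized recommendations.

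**What to change.** State that the exploratory predictor and responder models are fitted on both matched groups with group, factor and group-by-factor terms: linear for the WOMAC score, adjusted for its baseline value, and logistic for OMERACT-OARSI response. Report the interaction estimates with confidence intervals. Base any statement on who benefits from training on these interactions only, and call associations found within the intervention group prognostic.

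No new data are needed. The responder criterion is collected in both groups, and age, gender, baseline WOMAC scores and self-efficacy are already inputs to the propensity score. The cost is that modest interactions will often be missed (about 43% power at 280 effective per group and 71% at 560 for an interaction of 0.3 SD), so fewer predictors will be claimed. Because the groups are not randomized, residual confounding can affect interactions too, and the report should say so.
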